**Limitations of the study**

- The number of study participants has been selected to test efficacy and feasibility to be able to perform a sample size calculation to determine the number of participants required for a definitive trial. Therefore, these results should be considered as preliminary findings.
- Study is conducted in a single tertiary hospital and therefore may need to be adapted prior to wider implementation.

**Impact of the study**

As this is a feasibility study, the impact of this study on patient care and NHS costs cannot be understood fully and may not change practice. However, if found successful further funding will be sought out for a future definite trial to test its effectiveness. A well-designed prehabilitation study will positively impact patient outcomes by improving strength and function and reducing anxiety prior to surgery thereby ensuring quicker recovery post-op. It is anticipated to reduce socio-economic burden by facilitating continuation or resumption of work and may reduce economic impact on services post-op (e.g., reduced need for physiotherapy follow-up and quicker discharge from the service). This study is conducted within a tertiary NHS setting and therefore can be reproduced and applied in similar healthcare settings.

**Funding**

This programme of research is conducted as part fulfilment of a PhD fellowship funded by the National institute for Health and Care Research, UK and hosted by Anglia Ruskin University, Cambridge, UK

**Competing interests**

None to declare

**Acknowledgements**

The authors would like to thank Physitrack PLC for permitting the use the images.

**Supporting information**

**Fig 1. Progression of Abductor strengthening exercise**

*Reprinted from****Physitrack PLC (***[***https://www.physitrack.com/***](https://www.physitrack.com/)*) under a CC BY license, with permission from****Physitrack PLC****, original copyright****2012***

Exercise

Progression

[figure not shown]

[figure not shown]

**Table 1. Study objectives and success criteria**

| General objectives | Success criteria |
| --- | --- |
| Recruitment procedure | Participants were recruited within the time constraints of the local NHS hospital |
|  | Participants report that there were no challenges with the recruitment procedure |
| Data collection methods | Data completeness of ≥80% |
|  | Patients and assessors reported that there were no challenges with the data collection methods |
| Follow-up procedures | 100% of participants were contacted for follow-up |
|  | ≥80% completion of follow-up outcome measures |
| Specific objectives | **Success criteria** |
| *Feasibility* | |
| Participant recruitment rates | The recruitment rate of this study will be considered sufficient if at least 33% of eligible patients are recruited over a period of 18 months (n=60). |
| Attrition rate | <30% dropout |
| Usability of Physitrack | Patients and Physiotherapists reported no challenges with the use of Physitrack and telehealth system. |
| Capacity (time and effort) of clinicians to deliver the programme | Physiotherapists report that they had adequate time and resources available to deliver the programme |
| Treatment fidelity | ≥80%  completion of the self-reported checklist |
|  | Physiotherapists reports that there were no barriers identified in the use of self-reported checklists. |
| *Suitability* | |
| Outcome measures | Patients and assessor report that the outcome measures were appropriate and self-explanatory |
|  | Data completeness of  ≥80% |
| Adherence to the programme | ≥70%  of the sessions (face to face + home ex monitored by Physitrack) |
| Time required to undertake each stages of the study | Physiotherapists report that they had enough time to complete each stages of the study. |
| Service infrastructure | Recruitment targets met  Data completeness of ≥80%  Clinicians and researchers report that there was adequate infrastructure to allow completion of a full trial. |
| *Acceptability* | |
| Intervention | Patients and clinicians report that the programme was appropriate and satisfactory |
| Randomisation | Patients are willing to be randomised for a future definitive trial.  (≥80% ) |
| Safety | |
| Intervention | Patients report that the intervention was safe, and no serious adverse events occurred during the prehabilitation phase. |

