**Use of Physitrack app and Telehealth system:**

Physitrack provides exercise information and videos via website and apps. Dosage and frequency of the exercises can be selected, and patients will be encouraged to record completion of the exercises enabling the physiotherapist to measure adherence via the app. Physitrack has been found to improve adherence and patient confidence and is utilised across several NHS Trusts in the UK [37]. Additionally, the use of Physitrack’s tele-rehabilitation would enable physiotherapists and patients to interact with each other via video providing reassurance of the correct exercise techniques and progression.

The participants in the intervention group will use Physitrack which provides photos and videos of the prescribed exercises and those unable to use the app will be provided with paper-based instructions. Additionally, patients will be asked to complete their exercises at home twice weekly.

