**Physiotherapists**

In-depth face to face semi structured interviews will be used to evaluate the views of the Physiotherapists (n=4) regarding the feasibility, suitability and acceptability of the intervention, outcome measures as well as the Physitrack app in an NHS setting as described below. The interviews will be conducted by the PI within one year of commencement of the study to gather qualitative data. Appropriate questions for the interviews will be developed by the PI and the supervisory team. A patient and public involvement group will review the questions for clarity and appropriateness [38].

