**Outcome measures**

**Feasibility measures**

Feasibility parameters will be utilised to answer the objectives as per Table 1. The recruitment rate will be determined by the number of participants who are eligible and consent to participate in the study. Attrition will be defined by the number of consenting participants who drop out during the study. Timing of dropouts and reasons (where provided) will be explored to determine if the follow-up points are appropriate prior to a definitive RCT. Follow-up rates and response rates to questionnaires will be collected at each follow-up point. The usability of the Physitrack app and tele-rehabilitation will be evaluated using a modified System Usability Scale (SUS)[25]. Time and effort of clinicians delivering the interventions will be captured via the hospital’s electronic system.

Treatment fidelity is the extent to which an intervention is delivered as per study protocol and is critical in the development and testing of evidence-based interventions [40]. Assessing fidelity in the feasibility stage is also critical to identify interventions that have lower than expected fidelity which can then be used to refine interventions prior to a full trial [41]. Fidelity will be monitored by analysing self-reported checklists completed by the treating Physiotherapists. A numerical rating scale (5 point Likert scale) will be used to measure content and quality of the interventions and post-session feedback will be given to the clinicians to improve treatment delivery [42]^.^

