**Sample Size**

An overall participant sample of 50-60 (25-30 per arm) is recommended to estimate standard deviations for calculating sample size required for a full trial [69]. As a tertiary referral centre for hip arthroscopies, 350-375 new patients are referred to the service every year out of which an estimated 120 hip arthroscopies are performed/year.

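### Table 1 judges Physitrack usability by an absolute absence of reported challenges and makes no use of the usability scale the protocol collects

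*Protocol*

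**What the plan says.** The Objectives section of the protocol places the success criteria in Table 1, and the Feasibility measures section ties the measures to that table: "Feasibility parameters will be utilised to answer the objectives as per Table 1".

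- **Physitrack usability.** Table 1 gives a single criterion: "Patients and Physiotherapists reported no challenges with the use of Physitrack and telehealth system".
- **Recruitment procedure.** One of two criteria is "Participants report that there were no challenges with the recruitment procedure". The other is that recruitment fitted the time constraints of the hospital.
- **Data collection methods.** One of two criteria is "Patients and assessors reported that there were no challenges with the data collection methods". The other is data completeness of at least 80%.

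The Feasibility measures section names the usability instrument: "The usability of the Physitrack app and tele-rehabilitation will be evaluated using a modified System Usability Scale (SUS)[25]". Table 1 contains no SUS score and no cut-off. The section on use of the Physitrack app adds that "those unable to use the app will be provided with paper-based instructions".

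Other Table 1 rows carry tolerances: at least 80% for completeness, follow-up measures, fidelity checklists and willingness to be randomised; at least 70% for adherence; under 30% for dropout.

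**The concern.** The specific objective is to evaluate how easy the app is to use, which is a matter of degree, and the protocol has chosen a graded instrument for it. The deciding criterion is nevertheless all-or-nothing and is not tied to that instrument. The named measure has no criterion, and the criterion has no named measure.

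Two things follow. Taken literally, the row depends on whether anyone mentions a difficulty, so the result moves with the number of people asked and how closely they are questioned. The qualitative component exists to refine the design before a full trial, so the problems it is meant to bring out would count against success. Taken as a general impression, the row has no rule for mixed reports, and whoever reads the transcripts decides the outcome afterwards.

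At stake is whether the usability verdict, and part of the verdicts on recruitment procedure and data collection, can be interpreted when the definitive trial is planned.

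**Working it through.** **Inputs from the protocol**

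- Sample Size: "An overall participant sample of 50-60 (25-30 per arm) is recommended to estimate standard deviations", so up to 30 prehabilitation patients.
- Physiotherapists (qualitative component): interviews to "evaluate the views of the Physiotherapists (n=4) regarding the feasibility, suitability and acceptability of the intervention", so 4 physiotherapists.
- Research participants (qualitative component): a focus group of 6 to 8 patients, with two or more sessions possible.
- Table 1: recruitment target of 60, being 33% of eligible patients over 18 months.

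**The plan's own figure.** Taking the roughly 120 hip arthroscopies a year in the Sample Size section as the eligible pool, 120 × 1.5 × 0.33 = 59.4. This agrees with the stated 60, which can serve as the largest denominator.

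**Assumptions.** The protocol gives no chance p that one person reports a challenge, so p is varied over 2%, 5% and 10%. Reports are treated as independent.

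**Literal reading.** The criterion is met only if none of the n people asked reports a challenge:

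P(pass) = (1 − p)^n

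| Row and people asked | n | p = 2% | p = 5% | p = 10% |
| --- | --- | --- | --- | --- |
| Usability: 30 patients + 4 physiotherapists | 34 | 50% | 17.5% | 2.8% |
| Usability: 25 patients + 4 physiotherapists | 29 | 56% | 23% | 4.7% |
| Usability: 8 focus-group patients + 4 physiotherapists | 12 | 78% | 54% | 28% |
| Recruitment wording: all participants | 60 | 30% | 4.6% | 0.2% |
| Recruitment wording: one focus group | 8 | 85% | 66% | 43% |

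For example, 0.95^34 = 0.175 and 0.95^12 = 0.540.

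For an 80% chance of meeting the usability criterion with n = 34, p must be no more than 1 − 0.8^(1/34) = 0.0065. That is, each person must have less than about a 0.65% chance of mentioning any challenge.

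**Effect of a proportion.** Suppose the recruitment wording required at least 80% of 60 participants to report no challenge, which is 48 or more. The binomial probability P(X ≥ 48), with X ~ Bin(60, 1 − p), is above 99.9% at p = 5%, 99.4% at p = 10% and 58% at p = 20%. Such a rule tolerates isolated difficulties but still responds to common ones. If only challenges that stopped or delayed participation are counted, p refers to those challenges and would be no larger.

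No SUS cut-off can be calculated, because the protocol states none.

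**The case against.** The best defence is that Table 1 speaks of patients and physiotherapists as groups and never says that every individual must be free of difficulty. Neighbouring rows on appropriateness and satisfaction have the same form, and a thematic analysis would report at that level. A reader might infer that one complaint forces a finding of failure. The protocol does not say so: it gives no rule for pooling reports and none for failing a row. This part of the defence stands. It does not rescue the criterion, because the group-level reading is unwritten and would be applied once the data are known.

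Three further stronger readings are also unsupported:

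- That the recruitment-procedure and data-collection rows can pass only with no challenges. Each has another criterion, and the table does not say whether both are needed.
- That the protocol forecasts app failures. The paper instructions are a contingency with no number attached, and someone given paper from the start need not report a challenge in using the app.
- That the usability objective cannot be answered at all. The SUS can still describe usability; it is simply tied to no success criterion.

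The larger denominators are also the least favourable ones. No section says that all 30 or all 60 people will be asked individually, and independence is doubtful within a focus group. The smaller denominators therefore belong beside the larger ones.

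It could also be said that a scoring cut-off belongs in an analysis plan. That would hold if the protocol were silent, but it sets the decision rule itself, in terms that do not match its chosen instrument.

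**Conclusion.** The point holds for the usability row: its sole criterion is absolute, undefined in proportion and severity, and detached from the modified SUS. On the literal reading, the chance of meeting it at p = 5% runs from 17.5% (34 people asked) to 54% (12 people asked). At p = 10% it runs from 2.8% to 28%. These figures rest on assumed values of p, on independence, and on denominators that the protocol leaves open. They show that missing the criterion is likely for a usable system if everyone is asked, not that it is certain.

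The recruitment-procedure and data-collection rows share the wording, but the weakness is smaller there because each has a second criterion. The SUS mismatch concerns the usability row alone. The study can run as planned and no treatment comparison is affected, but the usability verdict cannot be interpreted as written. The change should be made before Table 1 is used to judge feasibility.

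**What to change.** **Usability row.** Replace the criterion with a pre-specified cut-off on the modified SUS. Justify the cut-off for the modified scoring, since one published for the standard scale may not carry over. Judge it on prehabilitation participants. Report the physiotherapists' scores separately, because pooling four of them with the patients could hide a problem in either group. Report alongside it the proportion who needed paper instructions.

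**Recruitment-procedure and data-collection rows.** Replace the absolute wording with a pre-specified proportion reporting no challenge that stopped or delayed participation or completion. At least 80% is one example, being the level used in other Table 1 rows; those rows measure different things, so the choice needs a sentence of justification. State whether both criteria in each row must be met.

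**Qualitative data.** Use the interviews and focus groups to explain the results and refine the design, not as a zero-event rule.

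**Cost.** Table 1 is reworded and one or two closed questions are added to existing questionnaires, with no change to sample size, visits or intervention. The small downside is that the criteria will read as less demanding.

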**Specific objectives**

**Feasibility**

- To evaluate participant recruitment and attrition rates [24]
- To evaluate follow-up rates and response rates to questionnaires [24]
- To evaluate the ease of using the Physitrack app [25]
- To evaluate the time and effort of clinicians to deliver the intervention [24]
- To evaluate fidelity of intervention delivery [26]

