**Suitability**

- To evaluate suitability of the outcome measures [27]
- To evaluate participant adherence with prehabilitation interventions [24]
- To evaluate the time taken to undertake each phases of the study [24]
- To evaluate the appropriateness of incorporating a novel prehabilitation intervention for FAIS into the current NHS services infrastructure [28]

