**Randomisation and blinding**

Following baseline evaluation, participants will be randomly allocated to one of the two groups (prehabilitation or usual care) by the PI using a computer-generated random allocation sequence. This will be uploaded to a secure database known as REDCap (Research Electronic Data Capture) and all study personnel will be blinded to the allocation sequence ensuring adequate concealment [67, 68]. REDCap is a secure, web-based software platform designed to support data capture for research studies, providing 1) an intuitive interface for validated data capture; 2) audit trails for tracking data manipulation and export procedures; 3) automated export procedures for seamless data downloads to common statistical packages; and 4) procedures for data integration and interoperability with external sources.

Blinding participants and clinicians delivering interventions will not be possible as both will be aware of the intervention and allocation. However, the content of the programme will only be known to participants in the intervention group thereby reducing the risk of cross contamination between groups [34]. Physical outcome measures will be measured by a blinded assessor who will be trained by the PI to ensure standardisation and improve reliability of the assessment.

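### The Table 1 row on time per study stage rests only on the physiotherapists' opinion, so it cannot answer the objective of evaluating how long each phase takes

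*Protocol*

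**What the plan says.** The Suitability objectives include "To evaluate the time taken to undertake each phases of the study". The matching row of Table 1 has one criterion: "Physiotherapists report that they had enough time to complete each stages of the study".

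A separate Feasibility objective is "To evaluate the time and effort of clinicians to deliver the intervention". Its Table 1 criterion is "Physiotherapists report that they had adequate time and resources available to deliver the programme".

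On measurement, the Feasibility measures section states: "Time and effort of clinicians delivering the interventions will be captured via the hospital’s electronic system". The Suitability measures section adds that physiotherapists and participants will be asked about the time and effort of completing the outcome measures. The protocol describes no recording of how long any other stage takes.

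The physiotherapists' views are to be gathered in interviews (n=4) held by the PI within one year of the start of the study (Qualitative component, Physiotherapists).

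**The concern.** The objective is about time taken, but the criterion is about whether one staff group felt that time was sufficient. These are different quantities, and the second cannot stand in for the first when that group does not carry out most of the stages.

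The Participants section shows why stage times matter here. Patients are approached only if the surgical date leaves room for consent, randomisation and eight weeks of prehabilitation. How long those steps take, and where time is lost, is needed to plan the definitive trial. A favourable statement from the physiotherapists would close the row without supplying it. Because Table 1 itself fixes the criterion, this is not a detail left to a statistical analysis plan.

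**Working it through.** The plan gives no time figure for this row, so there is nothing to reproduce. The check sets the criterion against the described roles and the study timeline.

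**Who runs what.** The protocol does not list its stages; this listing is mine, from the activities it describes.
- Identifying patients: chief investigator or PI (Participants).
- Consent: PI or delegate, with an independent witness (Participants).
- Randomisation: PI (Randomisation and blinding).
- Education session: PI (Prehabilitation Intervention).
- Prehabilitation sessions, in clinic and remote: physiotherapists (Prehabilitation Intervention; Training of Physiotherapists).
- Physical assessments: "Physical outcome measures will be measured by a blinded assessor who will be trained by the PI" (Randomisation and blinding). The same section says that the clinicians delivering the interventions cannot be blinded, so the assessor is not one of them.
- Patient-reported outcomes: app or post (Trial component).

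The physiotherapists are described as running one of these activities. Table 1 names the assessor, clinicians and researchers separately in other rows, so the word physiotherapists in this row most naturally means those delivering the programme.

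**When they are asked.** Inputs: interviews by one year, about week 52; an 8-week programme before surgery; a last assessment at 12 months ± 4 weeks after surgery (Trial component). Assume the most favourable case: the first participant starts on day 1 and has surgery straight after the programme.
- Earliest opening of the 12-month window: 8 + 52 − 4 = week 56.
- Gap after the interview deadline: 56 − 52 = 4 weeks at the least.
- Recruitment runs for 18 months (Table 1), so it is still open at the interview deadline.
- A participant recruited at month 18 reaches 12 months after surgery at about 18 + 1.8 + 12 = month 31.8, where 1.8 months is the 8-week programme.

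If these interviews supply the report that Table 1 calls for, no participant can have reached the last stage when it is given.

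**What enters the rule.** The time row contains no duration, date or threshold. The only time described as recorded is that of clinicians delivering the intervention, and it enters neither the time row nor the capacity row. For the other stages no recording of duration is described.

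**The case against.** The strongest reply is that timing does not rest on this row alone, and much of that reply stands.
- Table 1 also requires recruitment within the hospital's time limits, at least 33% of eligible patients over 18 months, at least 70% adherence to sessions, all participants contacted for follow-up and at least 80% completion of follow-up measures.
- The service infrastructure row takes reports from clinicians and researchers.
- The Feasibility measures section examines when dropouts occur.

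These rows would show some lost time. They do not give time per stage or show where a delay arose, which is what the objective asks.

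A second reply is that the only numbered phases in the protocol are prehabilitation Phases 1 and 2, both delivered mainly by physiotherapists. On that reading they are largely the right people to ask. But the objective and the row both refer to the study, not the programme, and even on that reading the criterion evaluates no time taken.

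A third reply is that opinion-based criteria are a deliberate mixed-methods choice in a feasibility study. That is a good reason to keep the opinion, though not to make it the only input to an objective about time.

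Three stronger readings are tempting and are not supported.
- A reader might infer that the capacity row fails in the same way. It does not: it asks those who deliver the programme whether they had time and resources to do so, and their time is captured in any case.
- A reader might infer that programmes cut short by surgery would go unseen. The physiotherapists would see them, and missed sessions count against the adherence row.
- A reader might attach a probability to all four physiotherapists answering favourably. The protocol states no unanimity rule and gives no basis for such a probability, so no figure of that kind is offered.

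**Conclusion.** The concern holds for one row. As written, the row on time required for each stage can be declared met without any stage time being evaluated, on the report of staff described as running one of the listed activities and interviewed at least 4 weeks before any participant could enter the 12-month window.

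This rests on two assumptions: that physiotherapists in this row means those delivering the programme, and that the described interviews are the source of their report. If their report were gathered later, the timing point would fall away, but the mismatch between objective and criterion would remain.

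The consequence is an unanswered objective and weaker planning information for the definitive trial. It does not bias any clinical outcome. The change is worth making because it is cheap and specific.

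**What to change.** Base the time row of Table 1 on stage dates. Report:
- the median and range of days from information sheet to consent, consent to randomisation, randomisation to first session, and first session to surgery;
- the proportion of the prehabilitation arm completing the planned programme before surgery, with completion defined beforehand because the number of sessions is decided for each participant;
- the proportion of post-operative assessments falling inside the windows in the Trial component section (6 weeks, 6 months and 12 months, each ± 4 weeks).

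Any pass threshold should be set in advance by the team; the protocol gives no basis for a particular value here. Put the question about sufficient time to whoever runs each stage (PI and research team, assessor, physiotherapists), and use the answers to explain the recorded intervals.

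In the capacity row, keep the physiotherapists' report and present the clinician times from the hospital's electronic system beside it.

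The cost is revised wording in Table 1 and a short descriptive table, with no new visits. The team must confirm that the stage dates are recorded, since the protocol does not say so, and the result may be less favourable than an opinion-based pass.

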**Prehabilitation Intervention**

Interventions are described based on the Template for Intervention Description and Replication (TIDieR) [35]. The exercise intervention used in this study was developed utilising the findings of a systematic review on prehabilitation and an expert panel consensus methodology to define the core components of the intervention. The intervention will be delivered over a period of 8 weeks prior to surgery and will target 5 domains- muscle strength, range of motion, proprioception, cardiovascular fitness and addressing co-existing pathologies. Literature suggests high prevalence and poorer outcomes of depression and anxiety in people with FAIS [15, 36], and the intervention will therefore also include an in-person educational session delivered by the PI to provide greater understanding of the surgery to alleviate anxiety and help manage patient expectations. The intervention will include at least four in-clinic face-to-face sessions (once a fortnight) with an experienced physiotherapist (>2 years’ experience in treating musculoskeletal conditions including FAIS) followed by six to eight remotely monitored sessions (once a week) using a telehealth system. The number of sessions will be determined based on physiotherapist assessment and intensity and complexity of exercises will be gradually increased depending on each participant’s individual progress (Fig 1). Due to the wide variation of patient characteristics within the FAIS population (e.g. sedentary or athletic) interventions will be tailored according to individual participant’s capabilities.

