**Usual care intervention**

As per the host hospital’s current clinical guidelines, the usual care intervention consists of advice to continue with normal activities and no prehabilitation therapy.

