**Safety**

Safety of the interventions will be determined based on the number and nature of adverse events. All adverse events (related or unrelated to interventions) will be recorded. Components of the prehabilitation interventions are designed not to aggravate patient symptoms. However, in case of worsening of symptoms, the physiotherapist will re-evaluate and adapt the exercises to ensure safety.

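### The Table 1 safety criterion counts serious adverse events of any cause, so one unrelated event would fail the intervention on safety

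*Protocol*

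**What the plan says.** Safety is one of the four properties named in the Aim. Its only success criterion is the last row of Table 1, labelled Intervention, and it has two joint conditions: "Patients report that the intervention was safe", and "no serious adverse events occurred during the prehabilitation phase". The row states no relatedness condition, no arm and no comparison with usual care.

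The Safety paragraph under Outcome measures puts it differently: "Safety of the interventions will be determined based on the number and nature of adverse events". It adds: "All adverse events (related or unrelated to interventions) will be recorded".

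Three other places set the scale. Sample Size: "An overall participant sample of 50-60 (25-30 per arm) is recommended", for the purpose of estimating standard deviations. Prehabilitation Intervention: "The intervention will be delivered over a period of 8 weeks prior to surgery". Usual care intervention: the control arm receives "advice to continue with normal activities and no prehabilitation therapy".

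**The concern.** The protocol draws the line between related and unrelated events when it records them, and then drops it from the rule that decides success. A serious event with no connection to exercise or education (an accident or an acute illness, say) would count against the programme exactly as an exercise injury would. The criterion would then partly measure background illness in a small group over two months, not the safety of prehabilitation.

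At stake is one of the four headline answers that the study is meant to carry forward to a definitive trial. A control arm with the same wait and no prehabilitation could show the background rate, but the criterion does not refer to it.

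**Working it through.** **Plan's own figure.** The protocol gives no number for the safety criterion beyond zero events, so there is none to reproduce. The group size can be checked. Table 1 aims for 33% of eligible patients over 18 months, and Sample Size gives about 120 arthroscopies a year. If all of these are taken as eligible, 0.33 × 120 × 1.5 = 59.4, which agrees with the stated 60, or 30 per arm. Sample Size gives 25-30 per arm, so both ends are used.

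**Inputs.**
- n = 25 or 30 prehabilitation participants (Sample Size).
- Window: 8 weeks (Prehabilitation Intervention).
- Tolerated SAEs: 0, any cause (Table 1).
- p = risk per person of an unrelated SAE over the window. This is *not in the documents*; 0.1% to 2% is assumed.

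**Chance that a harmless intervention fails.** If prehabilitation causes no SAEs and participants are independent, P(at least one SAE) = 1 − (1 − p)^n.

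| Assumed p | n = 25 | n = 30 |
|---|---|---|
| 0.1% | 2.5% | 3.0% |
| 0.5% | 11.8% | 14.0% |
| 1% | 22.2% | 26.0% |
| 2% | 39.7% | 45.5% |

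For example, at p = 1% and n = 30: 1 − 0.99^30 = 1 − 0.740 = 0.260.

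**What a clean result supports.** This part needs no background rate. After 0 events in n, the exact upper 95% limit is 1 − 0.05^(1/n) one-sided and 1 − 0.025^(1/n) two-sided (Clopper-Pearson).

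| Observed | One-sided 95% | Two-sided 95% |
|---|---|---|
| 0/30 | 9.5% | 11.6% |
| 0/25 | 11.3% | 13.7% |

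**The case against.** - **Relatedness may already be intended.** The row is labelled Intervention, and the Safety paragraph looks at the nature of events, which leaves room to weigh cause. That is a fair reading of intent. But the criterion itself says that no serious events occurred, and nothing tells the reader to discount unrelated ones. If relatedness was meant, a few words settle it.
- **The background rate is assumed.** This stands. Participants are aged 16-50 and waiting for elective surgery, so a low rate is plausible. At 0.1% the chance of a false failure is only about 3%.
- **A zero-SAE rule is objective.** It is hard to manipulate, whereas relatedness would be judged unblinded at one site, where the principal investigator trains the physiotherapists and delivers the education session. This is a real cost. It is contained if SAEs of every cause are also shown by arm.
- **A reader might infer that one SAE would end the programme.** The documents do not support this. Table 1 lists success criteria and states no consequence of missing one.
- **A reader might infer that usual-care events also count, which would raise the failure risk.** That strains a row about the intervention and a phase that usual care does not have.
- **A reader might infer that the protocol treats zero events as proof of safety, or discards the control arm's events.** It does neither. In Table 1, being safe is what patients report. The Limitations section calls the results preliminary. The recording of adverse events is not restricted to one arm. Adverse event tables and intervals are commonly left to the analysis plan, so their absence is not a fault.

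**Conclusion.** The criterion as written can give a wrong answer: a single SAE unconnected with prehabilitation fails the intervention on safety, although the protocol itself distinguishes such events. With 30 participants and a harmless programme, the chance is about 3%, 14%, 26% or 45% at an assumed 8-week background risk of 0.1%, 0.5%, 1% or 2%. With 25 participants it is about 2%, 12%, 22% or 40%. These figures rest entirely on the assumed risk and on independence between participants. The inconsistency between Table 1 and the Safety paragraph does not.

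The limited meaning of a clean result is a minor wording point, not an error. Limits of roughly 10% to 14% after zero events follow from a sample sized for standard deviations, and the protocol claims no safety precision. The defect does not invalidate the trial, but it should be corrected because the repair is cheap.

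**What to change.** Restate the second condition in Table 1 as no SAE judged at least possibly related to prehabilitation, among participants allocated to prehabilitation, and say who makes that judgement.

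Alongside it, report all SAEs regardless of cause, by arm, over one pre-operative window defined identically for both arms (for example, from randomisation), since usual care has no prehabilitation phase of its own. The usual-care count then shows the background rate and lets a reader check the relatedness calls.

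As an optional wording change, state a clean result as 0 related SAEs in n participants with its exact upper limit.

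The cost is an edit to one table row and a relatedness field on the adverse event form, if it is not already there. The small downside is the unblinded relatedness judgement, which the by-arm count of all SAEs helps to check.
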